### **6.3 Time line**

This study will start 1 January 2016 and will continue until 275 patients are included. We expect to reach this amount round 1 January 2018. Data analyses (including one year follow up) are expected to be finished in 2019.

### **6.4 Withdrawal of individual subjects**

Subjects can leave the study at any time for any reason if they wish to do so without any consequences. The investigator can decide to withdraw a subject from the study for urgent medical reasons.

#### **Specific criteria for withdrawal**

Patients will be excluded from this study when they do not want to fill in questionnaires or do not want to visit our outpatient clinic during follow up.

Patients who are excluded after surgery or after discharge will be noted as 'lost to follow up'. They will not visit the 70PLUS outpatient clinic at 6 months or 12 months.

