## 4. STUDY POPULATION

### 4.1 Population (base)

All patients with gastro –intestinal carcinoma, who are diagnosed in the Amphia Hospital, Breda (clinically or outpatient clinic), will be discussed during a multidisciplinary meeting with gastroenterologist, GI- surgeon, radiologist and pathologist. Final treatment agreement and advice (if patient will be operated on) is made during this meeting.

All patients with aortic abdominal aneurysm, who are diagnosed in the Amphia Hospital, Breda (clinically or outpatient clinic), will be discussed during a multidisciplinary meeting with vascular surgeons and radiologist. Final agreement, if operation is needed, is made during this meeting.

During these meetings patients are selected to be included in our study. Next, either a gastro-enterologist or vascular surgeon will give written and spoken explanation about the study to obtain informed consent.

All patients of 70 years or older will be included in this study and seen at the 70 **PLUS** outpatient clinic. Both patients fit to wait for 5 weeks until surgery and patients who must be electively planned within 5 weeks will follow the pre-operative clinical pathway. (see figure).

This is done to obtain the best comparable population, in comparison with the retrospective population in which all patients are included with elective planned surgery of  $\geq 70$  years old

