**Exclusion criteria**

A potential subject who meets any of the following criteria will be excluded from participation in this study:

- all patients with moderate to severe cognitive impairment or dementia in medical history;
- emergent surgery (clinical conditions that mandate a surgery within 12 hours of admission);
- urgent surgery (clinical conditions that mandate surgery between 12 and 72 hours of admission);
- patients not willing to participate or to fill in the questionnaires;
- all patient who do not speak Dutch or English.

*Demented patients*

Demented patients are included as a subgroup. Demented patients are important to optimise due to their fragile state, functional dependency and poor nutritional status.

This patient group will undergo the same treatment as non-demented patients. However, we will take into account the capability of the patient to answer questionnaires and undergo the exercises. This will all be done in firm consultation with the first care giver. Informed consent is asked to the patient and first care giver.

However, severe demented patients are rarely operated on in case of AAA or CRC. The risk in these patients in elective setting is very high compared to the benefits, also these patient usually start having complaints in worse case and are often operated on in acute setting (which is an exclusion criterion in this study).

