**Sample size calculation**

To reduce the percentage of delirium from 15% to 7,5%, with a power of 80% with 5% two-sided significance level, a 50 -50 trial, needs 550 patients, or 275 patient per study arm.

We propose to make a comparison to a retrospective control group of patients studied between 2012 and 2014 in the Amphia Hospital, Breda. [1]

We aim to include 275 patients in the prospective study, which is feasible during approximately 2 years of accrual.

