### **6.5 Replacement of individual subjects after withdrawal**

Patients withdrawn from this study will not be replaced.

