### **6.6 Follow-up of subjects withdrawn from treatment**

Patients withdrawn from our study will follow usual follow up, only patient information about complications en mortality will be used.

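### Refusing questionnaires or visits excludes OUTO patients but cannot exclude historical controls; for those withdrawn, hospital and ICU stay are dropped and the fate of delirium data is unclear

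*Protocol*

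**What the plan says.** Three rules act on the OUTO group.

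- **At entry** (Exclusion criteria): the excluded include "patients not willing to participate or to fill in the questionnaires".
- **During the study** (Specific criteria for withdrawal): "Patients will be excluded from this study when they do not want to fill in questionnaires". Unwillingness to attend the later clinic visits has the same consequence. The same section foresees exclusion after surgery or after discharge; such patients are recorded as lost to follow-up and miss the 6- and 12-month visits. Section 6.5 adds: "Patients withdrawn from this study will not be replaced".
- **Data kept** (Section 6.6): for withdrawn patients, "only patient information about complications en mortality will be used".

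The controls are described differently. Section 3 says that the historical group completed no questionnaires. Section 4.1 explains that all patients aged 70 or older enter the pathway for the sake of comparability, "in comparison with the retrospective population in which all patients are included with elective planned surgery". Section 8 selects both groups by the same inclusion criteria and says nothing about exclusion or withdrawal rules.

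**The concern.** The primary outcome does not depend on questionnaires. Sections 6.2 and 8.1 take delirium from ward nurses' DOS scores, confirmed by a geriatrician. Hospital stay, ICU admission and ICU stay are also recorded during admission. Refusing a quality-of-life form or a later visit is therefore no reason to lose any of them.

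The rule can also take effect after the outcome has occurred. WHOQOL-BREF and MMSE are due at discharge (Section 6.2), directly after the period in which delirium is observed. If patients who have been delirious are less willing to complete them, exclusion would depend on the outcome, and in one group only. In a non-randomised comparison with historical controls, that would act directly on the primary result. The entry rule raises a related question about who is willing to take part.

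**Working it through.** **1. The plan's own figure.** The sample size section sets the aim: "To reduce the percentage of delirium from 15% to 7,5%, with a power of 80% with 5% two-sided significance level". With equal allocation it arrives at 275 in each group, 550 in all. With unpooled variance,

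n = (1.96 + 0.842)² × (0.15×0.85 + 0.075×0.925) / 0.075² = 274.7, or 275 per arm.

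The pooled formula gives 278, and power at 275 per arm is 79.6%. The stated size reproduces. It contains no allowance for withdrawal.

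**2. What happens to each outcome of a withdrawn OUTO patient under Section 6.6.**

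- Mortality and complications: kept.
- Hospital stay and ICU stay: not among the data kept. The secondary parameters list them beside the complication rate, not within it.
- Delirium: depends on the reading. Section 1 calls it a common complication, and Section 2 speaks of delirium and other complications, which makes it one of them. Section 6.7 lists its incidence separately from the complication rate, and the closing paragraph of Section 1 also names the two side by side.

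**3. Can the rule be mirrored in the controls?** No. They were never asked to complete questionnaires, so refusers among them cannot be identified.

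**4. Size, by assumption only.** The protocol gives neither a refusal rate nor the delirium risk of refusers. Assume no true effect, 15% delirium among all OUTO patients, and the delirium data of withdrawn patients discarded. If a fraction w is withdrawn and their risk is r, the rate among those left is

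(0.15 − w·r) / (1 − w).

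- w = 5%, r = 30%: (0.15 − 0.015)/0.95 = 14.2%, an apparent gain of 0.8 points.
- w = 10%, r = 30%: (0.15 − 0.030)/0.90 = 13.3%, a gain of 1.7 points.
- w = 10%, r = 40%: (0.15 − 0.040)/0.90 = 12.2%, a gain of 2.8 points.
- r = 15%, any w: 15.0%, no bias.
- w = 10%, r = 10%: (0.15 − 0.010)/0.90 = 15.6%, a bias against OUTO of 0.6 points.

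A gain of 0.8 to 2.8 points is 11% to 37% of the 7.5-point target. In an unadjusted comparison of two proportions with 275 controls, the chance of a significant result favouring OUTO would rise from 2.5% to 4.4% (w = 5%, r = 30%) or 7.8% (w = 10%, r = 30%).

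**5. Power.** If 5% or 10% of OUTO patients are lost without replacement and the true rates are 15% and 7.5%, power falls from 79.6% to 78.5% or 77.2%. This effect is small.

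**The case against.** A reader might infer that the protocol removes delirious patients from the primary analysis and so builds in a false benefit. The document does not support that, for several reasons.

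- Nowhere does it say that delirium already recorded on the ward is deleted. For patients excluded after surgery, the stated consequences are the lost-to-follow-up label and the missed later visits. Sections 1 and 2 support counting delirium among the complications that Section 6.6 keeps. This stands: loss of the primary outcome is one reading, not a stated fact.
- It contains no data on refusers. The withdrawal rule concerns unwillingness, not inability, and for patients with dementia the protocol says that their capability to answer will be taken into account. Refusers at entry could be fitter patients avoiding a daily exercise and diary programme. This stands too: neither direction nor size is established.
- A reader might also attribute a large bias to the entry criterion. Most refusal at entry would be refusal of consent, which no change to the questionnaire wording removes.
- The controls are not wholly unselected. They are restricted by age, indication and elective surgery; what they escape is selection by consent and by questionnaire refusal.
- Section 8 adjusts for many covariates and plans multiple imputation. This helps only in part: imputation is not stated to cover excluded patients, and adjustment for baseline covariates does not repair exclusion that depends on the outcome itself.

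What remains is a one-sided rule that serves no purpose for the primary outcome, and a retention clause that leaves that outcome's fate to interpretation.

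**Conclusion.** The point holds as a one-sided exclusion with an unclear retention rule. On the text, hospital stay and ICU stay of withdrawn OUTO patients are lost, and whether their delirium outcome is used depends on whether delirium is classed as a complication. Bias follows only if refusal is related to delirium risk or to having had delirium. The fall from 15% to between 14.2% and 12.2% rests wholly on the assumed 5-10% withdrawal, the assumed 30-40% risk, and the reading under which the delirium data are discarded. With a 15% risk in refusers the bias is zero, and with a lower risk it reverses. This is a cheap improvement, not a demonstrated bias in the primary comparison.

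**What to change.** Four changes of wording:

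1. In the exclusion criteria, delete the clause on unwillingness to complete questionnaires and keep unwillingness to participate.
2. In the specific criteria for withdrawal, state that refusing a questionnaire or a visit ends that measurement only.
3. In Section 6.6, name delirium, hospital stay and ICU stay among the data kept, unless consent for data use is withdrawn.
4. State that the primary delirium analysis includes every consented OUTO patient who undergoes the elective surgery, whatever their questionnaire or visit completion. The restriction to operated patients matters because the comparison group consists of patients who had elective surgery.

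Non-consent at entry remains a limitation. Report the number of eligible patients who decline and whatever characteristics of them are available.

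The cost is revised protocol and consent wording, plus some missing questionnaire data, for which Section 8 already plans multiple imputation. No extra patients or procedures are needed.

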### **6.5 Replacement of individual subjects after withdrawal**

Patients withdrawn from this study will not be replaced.

### **6.6 Follow-up of subjects withdrawn from treatment**

Patients withdrawn from our study will follow usual follow up, only patient information about complications en mortality will be used.

### **6.7 Premature termination of the study**

Study will be terminated in case of a higher complication rate or mortality compared to former research done. [1] After one year, analysis will be done to investigate if no negative effect occurs due to this study, this is done by comparing complication rate, incidence of delirium, rate of ICU admission, length of hospital stay and mortality within 6 months, with the historical patient group.

Also we will investigate the use and efficiency of iron injection in anaemic patients.

Interim analyses are not possible due to the small amount of patients gathered. No significant data can be obtained.

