**Flowchart Inclusion of patients**

[figure not shown]

We assume to be able to include 275 patients over a period of two years, starting 1 January 2016 until 31 December 2017. About 20% of these patients will be included for an abdominal aortic aneurysm and 80% for gastro –intestinal carcinoma. [1]

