### 8.4 Interim analysis (if applicable)

Interim analysis is not possible, because at that point, not enough patients will be gathered to obtain any significant value.

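### Section 6.7 ends the study for any higher complication rate or mortality, with no margin; read literally at one year, chance alone stops a neutral programme about 65 to 76% of the time, while 6.7 and 8.4 call interim analysis impossible

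*Protocol*

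**What the plan says.** Protocol section 6.7 opens with a mandatory rule: "Study will be terminated in case of a higher complication rate or mortality compared to former research done". The comparator in that sentence is reference 1 of the protocol. The section then schedules a look: "After one year, analysis will be done to investigate if no negative effect occurs due to this study". That look covers complications, delirium, ICU admission, "length of hospital stay and mortality within 6 months, with the historical patient group". The section closes with "Interim analyses are not possible due to the small amount of patients gathered. No significant data can be obtained", and section 8.4 repeats: "Interim analysis is not possible, because at that point, not enough patients will be gathered to obtain any significant value".

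No other section defines what counts as higher. Section 7.1 is a separate, general clause under which the sponsor suspends the study on safety grounds. It supplies no threshold for 6.7.

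**The concern.** The rule is binding, joins two outcomes by *or*, and is met by any excess, however small. When the true rates are equal, each comparison is close to a coin toss, so the chance that at least one goes the wrong way is well above one half.

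The section also asks for a between-group comparison that informs termination, at a point where the protocol itself says the data cannot support an interim analysis. If the rule is followed, a harmless or useful programme is likely to be ended by chance. If it is set aside because of 8.4, whoever decides at one year does so after seeing the data and without a stated criterion.

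**Working it through.** **Design figure.** The protocol's only design figure reproduces. It plans "To reduce the percentage of delirium from 15% to 7,5%, with a power of 80% with 5% two-sided significance level" and concludes "a 50 -50 trial, needs 550 patients, or 275 patient per study arm". With unpooled variances, n = (1.96 + 0.8416)² × (0.15×0.85 + 0.075×0.925) / 0.075² = 7.849 × 0.196875 / 0.005625 = 274.7, so 275 per arm. The sample size is not in question.

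**Inputs for the one-year look**
- Accrual: "We assume to be able to include 275 patients over a period of two years, starting 1 January 2016 until 31 December 2017". If even, 275/24 × 12 = 137.5, so about 137 patients at one year.
- Patients with 6 months of follow-up at one year: 275/24 × 6 = 69 counted from inclusion. Allowing about 1.15 months (5 weeks) from inclusion to surgery, 275/24 × 4.85 = 56.
- 6-month mortality: the Introduction gives 15% delirium, with mortality 20% with and 3% without it. Overall, 0.15×0.20 + 0.85×0.03 = 5.55%. Expected deaths are 56 × 0.0555 = 3.1 to 69 × 0.0555 = 3.8.
- Complication rate: not given in the protocol; assumed 20 to 50%.
- Controls: 275 or, as an alternative, a fixed published rate.

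**No true difference.** For each outcome, P(higher) is the probability that a/n₁ > b/275, with a and b binomial at the same rate. If the outcomes are independent, P(either) = 1 − (1 − P_c)(1 − P_m).

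| Case (complication rate 40%) | P_c | P_m | P(either) |
|---|---|---|---|
| 137 vs 275; mortality on 55 patients | 0.50 | 0.45 | 0.73 |
| 137 vs 275; mortality on 137 patients | 0.50 | 0.52 | 0.76 |
| 137 vs a fixed rate, both outcomes | 0.52 | 0.49 | 0.76 |

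Against 275 controls, moving the complication rate from 20 to 50% changes P(either) by less than 0.01. The two outcomes will be positively correlated, which lowers the figure. With patient-level correlation of 0 to 0.3, it is 0.68 to 0.76. If every death also counts as a complication, it is 0.66 to 0.72. A normal approximation, 3/4 − arcsin(ρ)/(2π), agrees: 0.75 at ρ = 0, 0.70 at ρ = 0.3, 0.67 at ρ = 0.5. A wider grid (69 to 275 patients, mortality 3 to 10%) spans about 0.61 to 0.78.

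**True benefit.** If delirium fell to 7.5% at the same conditional mortality, 6-month mortality would be 0.075×0.20 + 0.925×0.03 = 4.28%. With mortality on 55 patients, P_m = 0.30. The stop probability then depends on the assumed change in complications:

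| Complications | P(stop) |
|---|---|
| 40% to 30% | 0.31 |
| 40% to 35% | 0.41 |
| 40% to 38% | 0.54 |
| unchanged at 40% | 0.65 |

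A 10% relative reduction in both outcomes (complication rate 30% assumed, mortality on 137 patients) gives 0.48 to 0.55.

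**What a statistical criterion would do.** As an illustration only, suppose termination is considered when the one-sided 95% lower bound of the difference (unpooled variance) exceeds zero, with 137 vs 275 patients. At 40% complications and 3% short-term mortality (both assumed), the false-stop rate is about 0.05 and 0.03 per outcome, so 1 − 0.95×0.97 ≈ 0.08 for either. A doubling of short-term mortality from an assumed baseline of 1 to 4% is detected only about 14 to 44% of the time.

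**The case against.** **The rule may not be mechanical.** The sentence on the one-year look asks whether a negative effect occurs because of the study, which implies judgement about cause. A numerical boundary is also often left to an analysis plan or monitoring charter, which is not at hand. This has some weight, and the percentages hold only on the literal reading. But the fault is not a missing detail: the protocol states a mandatory rule, and nothing in it says that a higher rate merely prompts review.

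**The interim conflict may be one of terms.** Both passages reject interim analysis because significance cannot be reached, which is compatible with a descriptive safety review. That narrows the conflict but does not remove it. The look is a between-group comparison, it includes the primary outcome, and it sits under a termination rule.

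**Stronger readings that the protocol does not support**
- *There is no safety check at all.* Section 7.1 still obliges the sponsor to suspend on safety grounds. Section 7.2 requires SAE reports to the ethics committee within 7 or 15 days, although deaths from the normal course of illness are exempt. Section 10.3 requires annual reporting of SAEs.
- *Two different comparators are named.* The rule cites reference 1, and the sample size section attaches the same reference to the retrospective control group. They may be one cohort under two labels, and the protocol alone cannot settle this.
- *A beneficial programme would be stopped at one specific rate.* The protocol gives neither a complication rate nor an expected reduction in it, so only a range is defensible.

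**Conclusion.** The point stands in this form: section 6.7 contains a binding termination rule without a threshold, and the one-year comparison that informs it conflicts with the statements in 6.7 and 8.4 that interim analysis is not possible. The missing threshold and the conflict need no calculation.

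On the literal reading, a neutral programme would be stopped about 65 to 76% of the time, and a beneficial one about 30 to 65%. These figures rest on a single look, even accrual, an assumed complication rate and, for the neutral case, true rates equal to the comparator. More looks would raise them. What is absent is a usable between-group harm criterion, not safety oversight as such. The primary endpoint, sample size and primary model are unaffected.

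**What to change.** Change the wording of sections 6.7 and 8.4:

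1. State that a numerically higher rate does not by itself terminate the study.
2. Describe the one-year look as a harm-only review against one named and fixed historical cohort. The cohort's dates need settling first: section 3 gives both March 2013 to March 2015 and 2013 to November 2015, and the sample size section gives 2012 to 2014.
3. Pre-state a statistical criterion for *considering* termination. The sponsor sets its level and reports both its false-stop rate for either outcome and its power to detect harm.
4. Report 6-month mortality with the number of patients who have reached 6 months (about 55 to 70 at one year, with about 3 to 4 deaths expected).
5. State that there is no stopping for efficacy, and bring the last lines of 6.7 and section 8.4 into line with this review.

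The one-year comparison is already planned, so the change costs wording and a short calculation. The real downside is that any criterion strict enough to avoid chance stops has low power for rare events, as the 14 to 44% figure shows. It should therefore support judgement and the suspension clause in 7.1, not replace them.

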## **7 SAFETY REPORTING**

### **7.1 Temporary halt for reasons of subject safety**

In accordance to section 10, subsection 4, of the WMO, the sponsor will suspend the study if there is sufficient ground that continuation of the study will jeopardise subject health or safety. The sponsor will notify the accredited METC without undue delay of a temporary halt including the reason for such an action. The study will be suspended pending a further positive decision by the accredited METC. The investigator will take care that all subjects are kept informed.

### **7.2 AEs, SAEs and SUSARs**

#### **Adverse events (AEs)**

Adverse events are defined as any undesirable experience occurring to a subject during the study, whether or not considered related to trial procedure. All adverse events reported spontaneously by the subject or observed by the investigator or his staff will be recorded.

